### **Enhanced observation**

Some patients with CC-NAFLD may have elevated liver function tests at baseline. Participant will enter into enhanced observation as per the algorithm in Appendix D. Enhanced observation will include:

- Repeating a blood test to assess ALT, ALP, total bilirubin, INR within 5 days of results.
- Obtaining a more detailed history of symptoms and prior or concurrent disease.
- Obtaining a history of concomitant drug use (including non-prescription medications and herbal and dietary supplement preparations), alcohol use, recreational drug use, adherence to the dietary intervention (including consumption of regular foods).
- Obtaining a history of exposure to environmental chemical agents.
- Ruling out other causes of liver disease as needed (obtain viral hepatitis panel, imaging for evaluation of biliary tract disease, etc, if required in the opinion of a medically qualified investigator).
- Continue to monitor the above tests weekly until the tests have fallen below the triggering threshold and then monthly for 2 months, and then as per protocol and until the end of the 24-week follow-up.

During enhanced observation, the intervention can be continued, if desired and results do not trigger intervention discontinuation (Appendix E), at the discretion of a medically qualified investigator.

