| Co-primary Objectives
i. To assess the safety signals of the intervention

ii. To assess the potential efficacy of the intervention in improving a marker of liver inflammation/fibrosis

iii. To assess the potential efficacy of the intervention in not worsening MRE-estimated liver stiffness, a marker of fibrosis                                                                                                 | i. Criteria of severe changes in biochemistry (ALT, AST, total bilirubin)

ii. Iron-corrected T1 relaxation time (cT1) values by magnetic resonance imaging (MRI)

iii. Liver stiffness by magnetic resonance elastography (MRE)                                                                                                                                                        | 0, 2, 4, 16, & 24

0 & 24

0 & 24                                                                                                                                                                       |
| Secondary Objectives
To examine changes in liver stiffness by transient elastography

To examine changes in liver fat

To examine changes in blood biomarkers

To examine changes in physical performance

To examine adverse events

To examine changes in weight

To examine changes in total fat-free mass

To examine changes in visceral fat

To examine changes in muscle mass | Liver stiffness by transient elastography

i. Proton density fat fraction (PDFF)
ii. Controlled attenuation parameter

i. ELF
ii. UKELD score
iii. CP score

i. Physical performance test
ii. Liver frailty index

Adverse events

Body weight

Total fat-free mass on bioelectrical impedance

Visceral fat on MRI

Muscle mass on MRI | 0, 16, & 24

0 & 24
0, 16, & 24

0 & 24
0, 4, 16, & 24
0, 4, 16, & 24

0 & 24
0 & 24

0, 2, 4, 16, & 24

0, 4, 16, & 24

0, 4, 16, & 24

0 & 24

0 & 24 |

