## Abbreviations:

ALT: Alanine transaminase

AST: Aspartate transaminase

ULN: Upper limit of normal

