## 24. APPENDIX E: INTERVENTION DISCONTINUATION ALGORITHM

[figure not shown]

\* Unless the participant has Gilbert's syndrome in which case a conjugated bilirubin > 2x baseline will be used instead of total bilirubin.

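### The enhanced-observation retest panel in section 10 omits AST, and conjugated bilirubin for Gilbert's syndrome, although the protocol's own safety algorithms refer to both

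*Protocol*

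**What the plan says.** Protocol section 10, under Enhanced observation, sets entry by algorithm: "Participant will enter into enhanced observation as per the algorithm in Appendix D". The first step is "Repeating a blood test to assess ALT, ALP, total bilirubin, INR within 5 days of results". The last step refers back to that list: "Continue to monitor the above tests weekly until the tests have fallen below the triggering threshold", after which the checks become monthly for two months and then follow the ordinary schedule. The diet may go on meanwhile "if desired and results do not trigger intervention discontinuation (Appendix E"), at the discretion of a medically qualified investigator.

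Elsewhere the protocol relies on a different set of markers:

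- Section 6 defines co-primary outcome i by "Criteria of severe changes in biochemistry (ALT, AST, total bilirubin").
- The keys printed under the Appendix D and Appendix E figures each contain the entry "AST: Aspartate transaminase".
- A footnote to Appendix E says that, for participants with Gilbert's syndrome, "a conjugated bilirubin > 2x baseline will be used instead of total bilirubin". The bilirubin exclusion in section 8.3 lets such patients in, provided their conjugated bilirubin is normal.
- Section 9.6.3 lists AST and both total and conjugated bilirubin among the routine study analyses.

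**The concern.** The one list in section 10 serves three purposes: to confirm a signal, to decide when it has cleared, and to supply the results that are read against the discontinuation algorithm. A list that lacks a marker used by the algorithms cannot serve any of these purposes for that marker.

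This matters more here than in most trials. The study exists to find out whether rapid weight loss harms a cirrhotic liver, and section 5 expects early, transient aminotransferase rises. The useful distinction is between a rise that settles and one that persists, and repeat values of the marker that rose are what separate the two. Section 10 also asks the TSDMEC to classify possible acute liver dysfunction, with one category for insufficient data. Section 9.10 has a rule for elevations that persist when the diet is re-introduced. Both depend on repeat biochemistry.

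**Working it through.** The plan states no figure to reproduce. The check is a comparison of passages, plus the interval between scheduled AST measurements.

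**1. Markers named in each place**

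| Place in protocol | ALT | AST | ALP | Total bilirubin | Conjugated bilirubin | INR |
|---|---|---|---|---|---|---|
| Section 10, retest and weekly checks | yes | **no** | yes | yes | **no** | yes |
| Section 6, co-primary outcome i | yes | yes | no | yes | no | no |
| Appendix D, abbreviation key | yes | yes | not named | not named | not named | not named |
| Appendix E, key and footnote | yes | yes | not named | yes | yes (Gilbert's only) | not named |
| Section 9.6.3, routine analyses | yes | yes | yes | yes | yes | yes |

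The two appendix rows show only what the keys and the footnote reveal. The figures may name further markers.

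**2. The clearing rule applied to AST.** Assume that a participant enters enhanced observation on AST alone, which the visible text neither confirms nor excludes. The listed retest is ALT, ALP, total bilirubin and INR. None of these need ever have been above a triggering threshold. The rule is then either met at the first retest or has nothing to act on, while AST has not been looked at again. If entry requires AST together with ALT, the rule works for the ALT part only.

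**3. The Appendix E check for Gilbert's syndrome.** This part rests on visible text. Appendix E replaces total by conjugated bilirubin for these participants, and section 10 retests total bilirubin only. The mandated panel thus supplies the marker that Appendix E sets aside for them and leaves out the one that it uses.

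**4. Whether another passage closes the gap.** The Appendix B row containing AST is marked at screening, at baseline (if the screening sample is more than 28 days old) and at weeks 2, 4, 16 and 24. It has no mark in the ad-hoc visit column. Section 10 is therefore the only place that specifies the extra blood tests.

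**5. Interval to the next scheduled AST.** Inputs are the visit weeks and windows in section 9.8: week 4 ± 1 (3 to 5), week 16 ± 2 (14 to 18) and week 24 ± 3 (21 to 27).

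- Week 4 to week 16: nominal 16 − 4 = 12 weeks; shortest 14 − 5 = 9; longest 18 − 3 = 15.
- Week 16 to week 24: nominal 24 − 16 = 8 weeks; shortest 21 − 18 = 3; longest 27 − 14 = 13.
- Week 2 to week 4: nominal 4 − 2 = 2 weeks.

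Nominally, the longest of these gaps lies wholly within the sole-source diet phase (weeks 0 to 16, section 9.6.1).

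**The case against.** The strongest reply is that the list is incomplete rather than restrictive. Section 10 says what enhanced observation will include and does not bar further tests. Taken as a whole, a rule to monitor until results drop below the triggering threshold implies looking at whatever did the triggering. AST and conjugated bilirubin are in the routine analyses, ad-hoc visits are allowed, and a medically qualified investigator decides on continuation. ALT, ALP, total bilirubin and INR are still checked weekly. Moreover, the Appendix D and E figures are not available: AST might act only in combination with other markers, and a figure might state its own repeat tests.

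Much of this stands, and it rules out several stronger conclusions that a reader might draw:

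- **That an AST signal cannot be confirmed, cleared or escalated at all.** Not supported. AST is measured at the scheduled visits and may be added at any time. The documents show only that it is not required in between.
- **That the co-primary outcome has a hole, worth 1/16 = 6.25 percentage points per unresolved intervention case.** Not supported. The outcome is assessed at weeks 0, 2, 4, 16 and 24, all of which keep AST, and nothing makes it depend on the retests.
- **That TSDMEC reports would lack the triggering marker.** Not supported. The triggering value from the scheduled visit is available, and section 13.3.2 lets the committee request specific analyses. At most a repeat value is missing.

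The reply does not remove the mismatch itself. A site that carries out the written panel complies with section 10 and still lacks results that the protocol's own rules need. For Gilbert's syndrome this follows without any inference from a figure.

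**Conclusion.** The point holds as an internal contradiction with a bearing on participant safety. The mandated retest panel does not contain AST, or conjugated bilirubin in Gilbert's syndrome, so the clearing rule and the Appendix E check cannot be applied to those markers from that panel. An AST rise found at week 4 could go without a required repeat for 12 weeks (9 to 15 within the windows); one found at week 16, for 8 weeks (3 to 13).

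The AST part assumes that AST has a working role in the Appendix D and E algorithms. Its entry in both keys makes this very likely, but thresholds and combinations cannot be seen. The conjugated bilirubin part needs no such assumption, but it concerns only the bilirubin element of Appendix E, and the documents do not say how many of the 24 participants, if any, would have the syndrome. What is lost is the course of a signal between visits; the scheduled safety outcome stays intact.

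**What to change.** Reconcile the section 10 retest and weekly panel with Appendices D and E, the routine panel in section 9.6.3 and co-primary outcome i, so that the retest covers the markers on which the sponsor's own algorithms rely, including the Gilbert's footnote. If a marker was left out on purpose, section 10 should say so and state how the clearing and discontinuation rules then apply to it. Appendix B could carry a matching note for ad-hoc blood tests. Thresholds, discontinuation criteria and management rules remain for the sponsor to set.

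The cost is a short amendment and a few extra assays on blood already drawn under enhanced observation. Both assays are already among the routine study analyses, and no extra visit or sample is needed.

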### **Acute liver dysfunction**

Due to the challenge of recognizing and diagnosing acute liver dysfunction in subjects with pre-existing liver dysfunction, the TSDMEC will review potential cases of acute liver dysfunction and classify them as:

- Acute liver dysfunction attributable to the intervention could be excluded (there is a clear alternative explanation)
- Acute liver dysfunction attributable to the intervention could not be excluded (there is no clear alternative explanation)
- Indeterminate due to insufficient data.

## **10.1. Definition of Serious Adverse Events**

A serious adverse event is any untoward medical occurrence that:

- results in death
- is life-threatening
- requires inpatient hospitalisation or prolongation of existing hospitalisation
- results in persistent or significant disability/incapacity
- consists of a congenital anomaly or birth defect.

Other 'important medical events' may also be considered a serious adverse event when, based upon appropriate medical judgement, the event may jeopardise the participant and may require medical or surgical intervention to prevent one of the outcomes listed above.

NOTE: The term "life-threatening" in the definition of "serious" refers to an event in which the participant was at risk of death at the time of the event; it does not refer to an event which hypothetically might have caused death if it were more severe.

#### **Pre-specified clinical events judged as SAEs**

As one of the aims of the trial is to assess whether the intervention prevents progression of compensated cirrhosis to decompensation, the following events will be judged as SAEs:

- At least one event of hepatic decompensation:
  - Jaundice
  - Ascites
  - Hepatic encephalopathy
  - Variceal haemorrhage
- Liver transplantation or qualification for liver transplantation, defined as a MELD score  $\geq 15$
- Hepatocellular carcinoma.

### **10.2. Reporting Procedures for Serious Adverse Events**

A serious adverse event (SAE) occurring to a participant will be reported to the REC that gave a favourable opinion of the study where in the opinion of the Chief Investigator the event was 'related' (resulted from administration of any of the research procedures) and 'unexpected' in relation to those procedures. Reports of related and unexpected SAEs will be submitted within 15 working days of the Chief Investigator becoming aware of the event, using the HRA report of serious adverse event form (see HRA website).

## **11. STATISTICS AND ANALYSIS**

A Statistical Analysis Plan (SAP) is to be produced separately.

### **11.1. Statistical Analysis Plan (SAP)**

The statistical aspects of the study are summarised here with details fully described in a statistical analysis plan that will be available from the time that the first participant is recruited. The SAP will be finalised before any analysis takes place.

### **11.2. Description of the Statistical Methods**

A table will present the baseline characteristics. This table will include age, sex, ethnic group, weight, BMI, education, marital status, smoking status, health conditions, alcohol consumption, liver markers, and summary of medication. Continuous variables will be summarised using means and standard deviations. Medians with interquartile ranges will be presented where appropriate. Categorical variables will be summarised using counts and percentages. Data will be analysed using appropriate statistical software.

All randomised participants be included in the main analysis. Missing data will be imputed using appropriate methodology. Data will be plotted in before-after plots and visually inspected for changes in continuous outcomes. The percentage of participants with evidence of worsening in each liver outcome and the extent of this worsening will be reported.

Given the sample size, it is expected that the data will not be normally distributed and the statistical power to detect differences beyond the primary outcome will be limited.

Descriptive statistics ((mean [SD], median [IQR], count [%])) on each outcome, as appropriate, will be presented stratified by baseline cT1, Child-Pugh score, MELD score, diabetes status, and median BMI.

Where appropriate, continuous endpoints will be assessed with linear mixed effects models adjusting for treatment group and baseline value and binary endpoints will be assessed with the Cochran–Mantel–Haenszel test.

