|                            | ii. To assess the potential efficacy of the intervention in improving a marker of liver inflammation/fibrosis                                   | ii. Iron-corrected T1 relaxation time (cT1) values by magnetic resonance imaging (MRI) | 0 & 24            |
|                            | iii. To assess the potential efficacy of the intervention in not worsening MRE-estimated liver stiffness, a marker of liver fibrosis            | iii. Liver stiffness by magnetic resonance elastography (MRE)                          | 0 & 24            |
| Secondary                  | To examine changes in liver stiffness by transient elastography                                                                                 | Liver stiffness by transient elastography                                              | 0, 16, & 24       |
|                            | To examine changes in liver fat                                                                                                                 | i. Proton density fat fraction (PDFF)                                                  | 0 & 24            |
|                            |                                                                                                                                                 | ii. Controlled attenuation parameter                                                   | 0, 16, & 24       |
|                            | To examine changes in blood biomarkers                                                                                                          | i. ELF                                                                                 | 0 & 24            |
|                            |                                                                                                                                                 | ii. UKELD score                                                                        | 0, 4, 16, & 24    |
|                            |                                                                                                                                                 | iii. CP score                                                                          | 0, 4, 16, & 24    |

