#### **9.4. Randomisation**

Consented participants will be individually randomised with a 2:1 allocation to receive either the intervention or care as usual through minimisation with a 20% random element. The two stratified variables are BMI ( $\geq$ / $<$  35 kg/m^2) and type 2 diabetes (yes/no), as these are prognostic factors of clinical outcomes.

Randomisation will occur after the baseline visit has been completed and a final check ensuring that all eligibility criteria have been met. To allow time for the analysis of the blood sample, the window between the end of the baseline visit and the randomisation will be within 24 hours.

The CI will programme the randomisation software (MinimPY). The software is validated and there will be no paper-based back-up randomisation procedure in case of emergencies. Upon completion of the baseline visit, the researcher carrying out the baseline visit will submit a request for randomisation via phone call to an independent researcher including the values of the stratification variables for the participant who completed the baseline visit. The independent researcher will run the minimisation software that will allocate the participant to one of the two groups and inform the CI of the group allocation over the phone. The CI will inform the participant of the group allocation over the phone, so that the participant does not need to return for a randomisation visit.

Allocation concealment is achieved by

- concealing the processes of recruitment, screening, and eligibility assessment from the researcher performing the randomisation centrally
- performing the randomisation following the baseline visit
- not carrying out baseline visits for additional participants during the run-in period between the baseline visit of a participant and their randomisation.

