### **11.3. Sample Size Determination**

An 88ms difference in cT1 (co-primary endpoint) is related with a 2-point change in the histological NAFLD activity score and a 1-point difference in histological ballooning (the main NASH feature). In our ongoing pre-post pilot of TDR in NASH with fibrosis stage 2-3 (LiFT), cT1 reduced by a median of 130ms (SD of change: 70ms) at 12 weeks with similar estimates among the few participants who have already completed the 24-week follow-up.

Given the more advanced stage of the disease, 22 participants (n=15 intervention, n=7 control) will allow detecting a more conservative between-group difference of 100ms (SD: 70ms) with 90% power at 5% level. Assuming approximately a 10% dropout at 24 weeks as we observed in LiFT, 24 participants are needed (n=16 intervention, n=8 control).

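### The stated model for continuous endpoints leaves out the two minimisation factors, so its intervals are too wide to the extent that those factors predict cT1

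*Protocol*

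**What the plan says.** Protocol section 9.4 has participants "individually randomised with a 2:1 allocation to receive either the intervention or care as usual through minimisation with a 20% random element". The two factors are BMI (at or above versus below 35 kg/m²) and "type 2 diabetes (yes/no), as these are prognostic factors of clinical outcomes".

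Protocol section 11.2 gives one model for continuous outcomes, to be used where appropriate: "continuous endpoints will be assessed with linear mixed effects models adjusting for treatment group and baseline value". Diabetes status and BMI appear elsewhere in that section only as strata for descriptive tables. Section 11.1 leaves the details to a separate SAP, which was not available for this review.

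The powered endpoint is cT1, measured at weeks 0 and 24 only (Synopsis and section 6). MRE stiffness and PDFF follow the same schedule. Section 11.3 states that 15 intervention and 7 control participants can detect "a more conservative between-group difference of 100ms (SD: 70ms) with 90% power at 5% level".

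**The concern.** Allocation and analysis do not match. The design forces balance on two variables because the protocol calls them prognostic, and the analysis then treats allocation as if it had been unrestricted.

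Under forced balance, the between-group estimate varies less from trial to trial than a model without the factors assumes. The variance due to the factors stays in the residual, the standard error is too large, and the true type I error falls below the nominal 5%. With 22 evaluable participants, the trial would gain precision through its allocation and then fail to report it on a co-primary endpoint.

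A named covariate set is a choice already made. A SAP that follows section 11.2 to the letter would carry the omission forward.

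**Working it through.** **Inputs.** From section 11.3: difference 100 ms, SD 70 ms, 90% power, 5% level, 15 + 7 evaluable, 24 randomised. From section 9.4: 2:1 minimisation on two binary factors with a 20% random element. Assumptions, because the protocol does not give them: a two-sided test; 70 ms as the residual SD after adjusting for baseline; R² from 0 to 0.40; and the shares of participants in each BMI and diabetes group.

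**The plan's own figure.** With 2:1 allocation, n(control) = (1.960 + 1.282)² × 70² × (1 + 1/2) / 100² = 7.7, so 8 + 16 = 24 evaluable against the 22 stated. At 15 + 7, SE = 70 × √(1/15 + 1/7) = 32.0 ms. Two-sided power is 87.7% by the normal approximation and 84.3% by the noncentral t. One-sided, the figures are 93.0% and 91.4%. The protocol does not state sidedness. This only fixes the starting level and is not the point made here.

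**Closed form, assuming perfect balance.** The 95% half-width is t(0.975, df) × 70 × √(1 − R²) × √(1/15 + 1/7). With baseline only, df = 22 − 3 = 19. With the two factors added, df = 17.

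| R² | Half-width, baseline only (ms) | Half-width, plus factors (ms) | Ratio | Power, baseline only | Power, plus factors |
|---|---|---|---|---|---|
| 0 | 67.1 | 67.6 | 0.99 | 84.1% | 83.7% |
| 0.10 | 67.1 | 64.1 | 1.05 | 84.1% | 87.3% |
| 0.20 | 67.1 | 60.5 | 1.11 | 84.1% | 90.8% |
| 0.40 | 67.1 | 52.4 | 1.28 | 84.1% | 96.7% |

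**Simulation of the actual allocation.** 24 participants are minimised 2:1 with the 20% random element and 22 are analysed by least squares. This allows for imperfect balance, so its gains are smaller than those above and should be preferred.

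| R² | Type I error, without | Power, without | Power, with |
|---|---|---|---|
| 0 | 4.8% | about 83% | about 82% |
| 0.10 | 4.0% | about 83% | about 84% |
| 0.20 | 3.4% | about 84% | about 88% |
| 0.40 | 1.9% | about 86% | about 95% |

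With the factors in the model, type I error stays at 4.7% to 5.0%. Independent repeats of the simulation moved individual power figures by up to about 2 points.

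**Mechanism.** Without the factors, the mean simulated half-widths are 67.0, 67.4, 67.6 and 68.1 ms. Dividing by t(0.975, 19) = 2.093 gives reported standard errors of about 32.0, 32.2, 32.3 and 32.5 ms. The actual SD of the estimate is 32.5, 31.0, 30.0 and 27.2 ms. The reported error stays flat while the true error falls. At R² = 0.20, adding the factors barely changes the actual SD of the estimate (30.0 to 29.6 ms) but cuts the mean half-width from 67.6 to 61.3 ms. Most of the gain is an interval that matches the precision already achieved.

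**The case against.** - **The benefit is unknown.** This stands. Section 9.4 calls the factors prognostic of clinical outcomes in general, not of week-24 cT1 given baseline cT1. At R² of 5% or less there is no gain in power.
- **The error is in the safe direction.** This also stands. The omission cannot create a false positive. Section 11.7 treats the intervals as nominal and descriptive, and progression under section 11.10 rests on recruitment, adherence, retention and adjudicated safety, not on a cT1 p-value.
- **Details belong in the SAP.** This stands for much of the model, but not for a covariate list that the protocol itself states.

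A reader might infer more than the text supports:

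- *That the protocol fits an inestimable random intercept to single-follow-up endpoints and so gives anti-conservative Wald-z results.* The mixed model applies only where appropriate. No random effect, software or degrees-of-freedom method is named, and a random effect for site is not excluded.
- *That the lack of a visit term blurs the week-24 effect.* cT1 and MRE have one follow-up, so this cannot happen to them. For repeated secondary outcomes, visit terms are ordinary SAP detail.
- *That the median BMI split in section 11.2 should be replaced by 35 kg/m².* It serves descriptive tables only and is a matter of preference.

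**Conclusion.** The point holds in a limited form. The protocol minimises on BMI group and diabetes as prognostic factors and states a model without them. The consequence is conservative inference. In closed form, the cT1 interval is about 5%, 11% or 28% wider than it need be at R² = 0.10, 0.20 or 0.40. In simulation, power is lower by about 1, 4 or 9 points at the same values, and type I error falls to about 2% at the top of the range. At R² = 0 nothing is lost by the omission.

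These sizes rest on an assumed R², a two-sided test, 22 evaluable participants and a residual SD of 70 ms. The direction follows from the design and does not depend on the exact R². It is worth correcting because the change is cheap, but it does not threaten the trial's validity.

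**What to change.** In section 11.2, and in the SAP to match:

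- For endpoints with a single follow-up (cT1, MRE stiffness, PDFF), state an ANCOVA of the week-24 value on arm, baseline value, BMI group (at or above versus below 35 kg/m²) and type 2 diabetes, with t-based confidence intervals.
- For endpoints with repeated follow-up, add the same two factors to the mixed model.

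The cost is a change of wording and two degrees of freedom, with no change to conduct or data collection. If the factors explain nothing, the loss for cT1 is 0.4 points of power in closed form (84.1% to 83.7%) and about 1 to 1.5 points in simulation. The relative cost is larger for MRE, which is done only at sites with the equipment and may have fewer participants.

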### **11.7. The Level of Statistical Significance**

The level of statistical significance will be set at  $p < 0.05$ . There will be no adjustment for multiple testing. The 95% confidence intervals will be presented but regarded nominal and descriptive.

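### If the Cochran–Mantel–Haenszel test at p<0.05 is used for the co-primary safety outcome at 16 vs 8, it is unreliable for rare events, and the power sentence wrongly implies that this outcome is powered

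*Protocol*

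**What the plan says.** Protocol section 6 lists three co-primary objectives. The outcome for the first, safety signals, is "i. Criteria of severe changes in biochemistry (ALT, AST, total bilirubin"), listed at weeks 0, 2, 4, 16 and 24. The other two are cT1 and MRE stiffness.

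Section 11.2 gives the between-group methods in one sentence. It opens "Where appropriate, continuous endpoints will be assessed with linear mixed effects models" and ends by saying that "binary endpoints will be assessed with the Cochran–Mantel–Haenszel test". It names no strata, continuity correction, exact version or effect measure, and does not mention the safety outcome by name. The same section plans to report the percentage of participants who worsen on each liver outcome.

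On power, section 11.2 states that "the statistical power to detect differences beyond the primary outcome will be limited". The only calculation is in section 11.3, for cT1, and ends with "24 participants are needed (n=16 intervention, n=8 control").

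Section 11.7 adds "The level of statistical significance will be set at" p<0.05 and "The 95% confidence intervals will be presented but regarded nominal and descriptive".

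**The concern.** Whether a participant met the severe-change criteria is naturally a yes/no outcome, and the Cochran–Mantel–Haenszel (CMH) test is the only between-group method the protocol names for such outcomes. CMH refers its statistic to a chi-square distribution, an approximation that needs reasonable expected counts. With 8 controls and events that one hopes are rare, those counts are close to zero.

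The lay summary says the trial is meant to find out whether rapid weight loss worsens the liver in these patients. Two misreadings are therefore at stake. A substantial excess of severe liver-test changes on the diet could be reported as not significant and taken as reassurance. Two chance events among controls could be reported as a significant safety advantage for the diet. The power sentence adds to the first risk, because it tells the reader that limited power is a problem only for outcomes other than the primary one.

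**Working it through.** **The plan's own figure.** For cT1 with 15 vs 7, a difference of 100 ms and an SD of 70 ms, SE = 70 × √(1/15 + 1/7) = 32.0 ms, and 100/32.0 = 3.12. Power at the 5% level is 87.7% (two-sided, normal), 84.3% (two-sided t) or 91.4% (one-sided t). The stated 90% is thus roughly reproduced; the protocol does not state sidedness. No corresponding figure exists for the safety outcome.

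**Inputs for the safety outcome.** Arms of 16 and 8 (11.3); p<0.05 (11.7), taken as two-sided; one met/not-met result per participant (my reading of section 6). Event rates are assumptions.

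**Formula, one stratum.** With a events on the diet and m events in total, E = 16m/24, V = m(24−m)·16·8/(24²·23), and χ² = (|a−E|−c)²/V on 1 df, with c = 0 (uncorrected) or 0.5 (corrected).

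- 0/16 vs 2/8: m = 2, E = 1.333, V = 0.425, so χ² = 1.333²/0.425 = 4.18 and p = 0.041.
- 6/16 vs 0/8: m = 6, E = 4, V = 1.043, so χ² = 2²/1.043 = 3.83 and p = 0.0502.
- 7/16 vs 0/8: m = 7, E = 4.667, V = 1.150, so χ² = 2.333²/1.150 = 4.74 and p = 0.030.

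| Diet vs control | CMH, c=0 | CMH, c=0.5 | Fisher exact |
|---|---|---|---|
| 0/16 vs 2/8 | 0.041 | 0.20 | 0.10 |
| 5/16 vs 0/8 | 0.082 | 0.22 | 0.13 |
| 6/16 vs 0/8 | 0.0502 | 0.14 | 0.066 |
| 7/16 vs 0/8 | 0.030 | 0.087 | 0.054 |
| 8/16 vs 0/8 | 0.016 | 0.051 | 0.022 |
| 9/16 vs 0/8 | 0.0086 | 0.029 | 0.0095 |

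With no control event, harm first reaches p<0.05 at 7/16 uncorrected, 9/16 corrected and 8/16 by Fisher.

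**Other layouts.** With 15 vs 7 the uncorrected pattern is the same: 0 vs 2 gives 0.034, 6 vs 0 gives 0.055 and 7 vs 0 gives 0.033. In the two- and four-stratum layouts tried, 0 vs 2 gives 0.025 to 0.046 uncorrected and 0.16 to 0.21 corrected. Strata can also lower the harm count: with strata of 12/6 and 4/2, the most favourable placement of 4 vs 0 gives p = 0.025.

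**Power to flag harm.** If the control rate is 0%, uncorrected power is P(X ≥ 7) for X ~ Binomial(16, p); corrected uses X ≥ 9, Fisher X ≥ 8.

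| Assumed rates | CMH, c=0 | CMH, c=0.5 | Fisher |
|---|---|---|---|
| 20% vs 0% | 2.7% | 0.15% | 0.7% |
| 25% vs 0% | 8.0% | 0.7% | 2.7% |
| 30% vs 0% | 17.5% | 2.6% | 7.4% |
| 40% vs 0% | 47% | 14% | 28% |
| 50% vs 0% | 77% | 40% | 60% |

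**Where false positives fall.** Summing over all 17 × 9 tables with an equal 10% rate in both arms, uncorrected CMH declares the diet safer with probability 3.6% and harmful with probability 0.02%. At an equal 5% rate the figures are 2.5% and below 0.01%.

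**What an interval would show.** Wilson limits are 0 to 19.4% for 0/16, 0 to 32.4% for 0/8 and 14.2% to 55.6% for 5/16. The Newcombe interval for the risk difference d is d − √[(p₁−l₁)² + (u₂−p₂)²] to d + √[(u₁−p₁)² + (p₂−l₂)²], where l and u are each arm's Wilson limits.

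- 0/16 vs 0/8: d = 0, interval −32% to +19%.
- 5/16 vs 0/8: d = 31.25%. Lower limit 0.3125 − √(0.171² + 0.324²) = −0.054; upper limit 0.3125 + 0.243 = 0.556. Interval −5% to +56%.

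**The case against.** The best defence is that section 11 presents itself as a summary, that its methods sentence is hedged, and that strata, correction and an exact version normally belong in a SAP, which is not shown. That stands: a reader might infer that the protocol fixes an uncorrected CMH test for the safety outcome, and it does not. But the hedge gives no criterion and no alternative, so the objection remains to the one method named.

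Other stronger readings also fail:

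- A reader might infer that 0 vs 2 would always be called significant. It would not; the correction moves p to 0.20.
- A reader might infer that the test almost never detects harm. That fits assumed rates up to about 25%, but not 40–50%, where uncorrected power is 47–77%.
- A reader might infer that the analysis breaks down, or that section 11.7's intervals cannot be produced, when controls have no event. The protocol promises no odds ratio, and a risk difference remains estimable.

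It is also fair that low power comes mainly from having 24 participants. Fisher's test does worse than uncorrected CMH for harm.

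Finally, this p-value decides nothing about safety. Section 11.10 leaves the safety progression criterion to the combined steering and monitoring committee. Section 13.3.2 gives that committee unblinded data and the biochemistry of participants who discontinue or are under enhanced observation, and section 10 requires laboratory abnormalities that trigger either to be recorded as adverse events. This limits the consequence, but does not protect the published result for the co-primary outcome.

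**Conclusion.** The concern holds in conditional form. If CMH at p<0.05 is applied to the safety co-primary at 16 vs 8, it is a poor guide in either version. Uncorrected, two control events against none suffice for a significant advantage, while seven diet events against none are needed to signal harm. Corrected, that asymmetry shrinks but harm needs nine. Non-significance here cannot be read as safety.

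The exact counts assume one stratum and one yes/no result per participant; the power figures rest on assumed rates. The power sentence needs neither assumption: section 6 has three co-primaries and section 11.3 sizes only cT1, so the sentence is wrong for the safety outcome as it stands.

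This should be corrected before analysis, but it is not critical to the trial's conduct, because the committee, not this test, adjudicates safety.

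**What to change.** In section 11.2, and in the SAP to match:

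1. Make estimation the primary presentation for the safety co-primary and other sparse binary endpoints. Give each arm's proportion with a Wilson interval, the method section 11.6 already uses, and the risk difference with a Newcombe or exact unconditional 95% interval.
2. If a p-value is kept, use an exact test and label it descriptive. Note that this removes the 0 vs 2 artefact (Fisher 0.10) but does not improve power for harm.
3. State that a non-significant result on this outcome is not evidence of safety.
4. Reword the power sentence to say that the stated power applies to cT1 only and that the safety co-primary is not powered.

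The cost is wording only, with no new data or participants. The price is a less favourable safety statement: even with no events in either arm, the report would have to show that the data are compatible with an excess of up to 19 percentage points on the diet.
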